### Sample size and power using adaptive design methods

This study will accrue 900 children (450 children per study arm) with pneumonia and high-risk comorbidities. Mortality assumptions for this study were derived from published literature and programmatic data from Malawi.

We estimate true mortality rates of 14.7% with standard care and 6.1% for bCPAP cases. With a 95% follow-up rate and α=0.05, the power (1 – β) is estimated to be 99%. Assuming mortality of 14.7% in the standard care arm, the sample is sufficient to reject the null hypothesis with 80% probability if the mortality rate in the bCPAP arm is 8.7% or lower.

The study cohort is further divided into two subgroups of high-risk conditions (figure 5). Distributions for subgroups were reassessed using adaptive design methods from data collected during the first 10 months of the study. All effect estimates were determined *a priori*.

**Figure 5 F5:**
[figure not shown]
Projected enrolment.

Severe hypoxaemia without comorbidity subgroup: 300 (150 per arm) children with severe hypoxaemia but without HIV infection, HUE or severe malnutrition.Power analysis subgroup 1: we estimate 13% mortality for standard care and 4% for bCPAP cases.^8^
With 95% follow-up, equal allocation to the standard care and bCPAP conditions, and the hypothesised true mortality rates described, these analyses are powered at 80%.
Comorbidity subgroup: 600 children (300 per arm) with HIV infection, HUE or severe malnutrition.Power analysis subgroup 2: we estimate 15.6% mortality for standard care and 7.1% for bCPAP cases based on relative contributions by each subgroup extrapolated from observational data. The observational data reveal approximately:10% of children are infected with HIV, with assumed standard care mortality of 30% and bCPAP mortality of 14%.^7 9^
30% of children have HUE, with assumed standard care mortality of 12% and bCPAP mortality of 5%.^7^
60% of children are severely malnourished (HIV uninfected and HIV unexposed), with assumed standard care mortality of 15% and bCPAP mortality of 7%.^5^

With 95% follow-up, equal allocation to the standard care and bCPAP conditions, and the hypothesised true morality rates described, these analyses are powered at 89%. Assuming mortality of 15.6% in the standard care arm, the sample is sufficient to reject the null hypothesis with 80% probability if the mortality rate in the bCPAP arm is 8.3% or lower.

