### Statistical methodology and analysis

Logistic regression will be used in the primary and interim outcome analyses. Hospital pneumonia outcome (pneumonia cure vs died) will be the primary endpoint; study arm (bCPAP vs standard care) will be the treatment variable in primary and interim outcome analyses.

We will employ the O’Brien-Fleming stopping rule to address any inflated type II error stemming from multiple comparisons.^25^ p Values (and Z-score cut-offs) for two-sided tests used in the first interim, second interim and final analyses will be .0006 (3.438), .0151 (2.431) and .0471 (1.985), respectively.^26^

If any significant imbalance between groups on baseline covariates is present then results of logistic regression analyses controlling for these variables will also be done. If missing data do not appear to be missing completely at random, multiple imputation methods will be used to model the missinginess mechanism based on observed data and to evaluate whether the study findings vary when accounting for missinginess.

Secondary analyses will examine whether treatment effect varies by baseline patient characteristics. As with the primary analyses, hospital pneumonia cure versus died before hospital pneumonia cure will be the outcome in logistic regression with independent variables including group assignment, patient characteristic and an interaction between group assignment and patient characteristic.

Separate models will be run for each patient characteristic of interest, including primary risk category—comorbidity (HIV infection or HUE, and/or severe acute malnutrition) and severe hypoxaemia. We will also examine whether severe hypoxaemia modifies the effect of treatment for children with a comorbidity through the use of interaction terms.

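### The two mortality rates said to be detectable with 80% power (8.3% comorbidity, 8.7% overall) do not hold under the 95% follow-up assumed beside them; the limits are about 8.0% and 8.6%

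*Protocol article*

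**What the plan says.** All the figures are in the protocol article, under the heading Sample size and power using adaptive design methods and in the subgroup text that follows Figure 5.

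- **Whole trial.** "This study will accrue 900 children (450 children per study arm"). "We estimate true mortality rates of 14.7% with standard care and 6.1% for bCPAP cases". The 99% power is given "With a 95% follow-up rate and α=0.05". The next sentence keeps standard-care mortality at 14.7% and says that the sample rejects the null "with 80% probability if the mortality rate in the bCPAP arm is 8.7% or lower".
- **Comorbidity subgroup.** "Comorbidity subgroup: 600 children (300 per arm) with HIV infection, HUE or severe malnutrition". At 15.6% versus 7.1% and 95% follow-up, power is given as 89%. The next sentence keeps 15.6% and says that the sample rejects "with 80% probability if the mortality rate in the bCPAP arm is 8.3% or lower".

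Neither limit sentence repeats the follow-up assumption or sets it aside. The section Statistical methodology and analysis makes the tests two-sided.

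**The concern.** In each pair of sentences, the first allows for 5% loss. A reader will take the second to rest on the same basis, but its limit is not reached once the loss is applied. In the comorbidity pair the change of basis is visible, because by the usual pooled-variance formula the 89% fits 285 per arm and not 300.

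These are the document's only statements of the smallest effect detectable with 80% power. Both err in the favourable direction, one for the primary comparison and one for the larger subgroup. Anyone using them to judge what a null result can exclude would credit the trial with slightly more sensitivity than it has.

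**Working it through.** **Inputs from the protocol.** 450 per arm overall and 300 per arm with comorbidity; 95% follow-up; 1:1 allocation; two-sided alpha 0.05; standard-care mortality 14.7% and 15.6%. Evaluable per arm: 450 × 0.95 = 427.5 and 300 × 0.95 = 285.

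**Formula.** The article names no power formula, so I start with the pooled-variance comparison of two proportions. With d = p1 − p2 and p̄ the mean of p1 and p2:

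A = √[2p̄(1 − p̄)], B = √[p1(1 − p1) + p2(1 − p2)], power = Φ[(d√n − 1.96A)/B].

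**Step 1. The plan's powers at the expected rates.**

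- Overall, 14.7% vs 6.1%, n = 427.5: A = 0.4317, B = 0.4274. (0.086 × √427.5 − 0.8461)/0.4274 = (1.7781 − 0.8461)/0.4274 = 2.181, power 98.5%. Exact enumeration of the chi-square test at 427 gives 98.8%. The stated 99% holds after loss.
- Comorbidity, 15.6% vs 7.1%, n = 285: A = 0.4486, B = 0.4446. (1.4350 − 0.8792)/0.4446 = 1.250, power 89.4%. At n = 300 it would be 90.9%. The stated 89% holds after loss.

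**Step 2. The overall limit, 14.7% vs 8.7%.** A = 0.4546, B = 0.4526, d = 0.060.

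- n = 450: (1.2728 − 0.8909)/0.4526 = 0.844, power 80.1%. The limit solves to 8.70%. This reproduces the plan's figure, with no loss.
- n = 427.5: (1.2406 − 0.8909)/0.4526 = 0.773, power 78.0%. The limit solves to 8.57%.

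**Step 3. The comorbidity limit, 15.6% vs 8.3%.** A = 0.4587, B = 0.4558, d = 0.073.

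- n = 300: (1.2644 − 0.8991)/0.4558 = 0.801, power 78.9%. The limit solves to 8.21%.
- n = 285: (1.2324 − 0.8991)/0.4558 = 0.731, power 76.8%. The limit solves to 8.04%.

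**Step 4. Does the choice of method matter?** Power at the stated limits, alpha 0.05 (exact column at 427 and 285 after loss):

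| Comparison | Evaluable per arm | Pooled | Unpooled | Arcsine | Exact chi-square |
|---|---|---|---|---|---|
| 14.7% vs 8.7% | 450 | 80.1% | 80.3% | 80.6% | 80.5% |
| 14.7% vs 8.7% | 427.5 | 78.0% | 78.3% | 78.5% | 78.5% |
| 15.6% vs 8.3% | 300 | 78.9% | 79.2% | 79.6% | 79.6% |
| 15.6% vs 8.3% | 285 | 76.8% | 77.2% | 77.5% | 77.4% |

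After loss, the 80% limits are 8.57% (pooled), 8.58% (unpooled) and 8.60% (arcsine) overall, and 8.04%, 8.07% and 8.11% for comorbidity. A Wald calculation on the log-odds scale and a continuity-corrected test give lower power still (75.4% and 72.6% for comorbidity at 285), so they do not rescue the stated limits. A one-sided 0.05 test overshoots (85.3% and 86.2%, pooled) and contradicts the two-sided testing in the plan.

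**Step 5. Does the stopping boundary change this?** The plan says that cut-offs for the first interim, "second interim and final analyses will be .0006 (3.438), .0151 (2.431) and .0471 (1.985"). At n = 427.5 and 14.7% vs 8.7%, the expected Z with unpooled variance is 1.2406/0.4526 = 2.741. A fixed test at 1.96 has power Φ(0.781) = 78.3%. A final look alone at 1.985 has Φ(0.756) = 77.5%. Simulating rejection at any of the three looks, with interims at 30% and 60% of enrolment as in Patient safety, gives 78.2%. The fixed 0.05 test is therefore a good stand-in for the whole sequential design.

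**The case against.** The strongest reply is that the sample in these sentences means the enrolled sample, with the follow-up condition belonging only to the sentence before. On that reading 8.7% is exactly right at 450 per arm, and 8.3% is a rounding matter at 300 per arm, where exact and arcsine power are 79.6% and the arcsine limit of 8.27% rounds to 8.3%. This has some force: the article never says that the limits include the loss, and the overall shift is only about 0.1 percentage point. But it leaves adjacent sentences on different bases with no signal to the reader. It also clears 8.3% only by rounding, since power at 300 per arm is 78.9% to 79.6%.

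It is also fair to say that a null result will be read from its confidence interval rather than from a planning figure, which limits the practical harm.

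Three stronger readings are tempting, and the documents do not support them.

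- *A reader might infer that the hypoxaemia-only claim ("hypothesised true mortality rates described, these analyses are powered at 80"%) is wrong too.* For 13% vs 4% at 142 to 143 per arm, the pooled formula gives 77.9% at 142, but exact enumeration gives 79.4% to 79.7% and arcsine 80.6% to 80.9%. The article names no formula, so the rounded 80% is defensible after loss.
- *A reader might infer that every figure should be recomputed at 0.0471.* That counts only the final look and understates power, as Step 5 shows. The article also does not say that the boundary governs the subgroup analyses.
- *A reader might infer that 8.3% is out of reach even with full follow-up.* The pooled formula does ask for 309 per arm, against 300 planned, but exact and arcsine power at 300 round to 80%. Omitted loss explains 8.7% fully and 8.3% only in part.

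**Conclusion.** The point holds as a minor arithmetic inconsistency. Under the section's own 95% follow-up and two-sided alpha of 0.05, power is about 77% at the stated comorbidity limit and about 78% at the stated overall limit. The 80% limits are about 8.0% to 8.1% and about 8.6%. The comorbidity figure is the firmer finding and the overall figure the milder one.

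The smallest detectable absolute difference grows from 15.6 − 8.3 = 7.3 to about 15.6 − 8.0 = 7.6 points for comorbidity, and from 14.7 − 8.7 = 6.0 to about 14.7 − 8.6 = 6.1 points overall.

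This rests on equal loss in both arms, a standard two-proportion test standing in for the logistic model, and the limit sentences sharing the follow-up assumption of the sentences before them. It does not show that the trial is underpowered at its expected rates, where 99% and 89% stand after loss.

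**What to change.** Put both limit sentences on the basis used for the 99% and 89%: 95% follow-up and two-sided alpha 0.05. Restate the detectable bCPAP mortality as about 8.0% in the comorbidity subgroup (285 evaluable per arm) and about 8.6% overall (about 427 per arm), and name the power formula. If complete follow-up was intended, say so; 8.7% may then stay, and 8.3% becomes about 8.2% by the pooled formula.

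Leave the hypoxaemia-only 80% and the alpha as they are. The cost is two edited sentences and slightly less favourable figures. Enrolment, tests and boundaries do not change.

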### Data collection, quality assurance and data management

All study staff are certified in Good Clinical Practice and were trained on study protocols and data collection. Staff complete refresher-training courses every 4–6 months and receive regular supervision.

Trial data are collected directly into a secure REDCap (Research Electronic Data Capture) database using encrypted tablets. REDCap is a secure, web-based application designed to support data capture for research studies. Paper case report forms are used for back-up when necessary.

### Statistical methodology and analysis

Logistic regression will be used in the primary and interim outcome analyses. Hospital pneumonia outcome (pneumonia cure vs died) will be the primary endpoint; study arm (bCPAP vs standard care) will be the treatment variable in primary and interim outcome analyses.

We will employ the O’Brien-Fleming stopping rule to address any inflated type II error stemming from multiple comparisons.^25^ p Values (and Z-score cut-offs) for two-sided tests used in the first interim, second interim and final analyses will be .0006 (3.438), .0151 (2.431) and .0471 (1.985), respectively.^26^

If any significant imbalance between groups on baseline covariates is present then results of logistic regression analyses controlling for these variables will also be done. If missing data do not appear to be missing completely at random, multiple imputation methods will be used to model the missinginess mechanism based on observed data and to evaluate whether the study findings vary when accounting for missinginess.

Secondary analyses will examine whether treatment effect varies by baseline patient characteristics. As with the primary analyses, hospital pneumonia cure versus died before hospital pneumonia cure will be the outcome in logistic regression with independent variables including group assignment, patient characteristic and an interaction between group assignment and patient characteristic.

Separate models will be run for each patient characteristic of interest, including primary risk category—comorbidity (HIV infection or HUE, and/or severe acute malnutrition) and severe hypoxaemia. We will also examine whether severe hypoxaemia modifies the effect of treatment for children with a comorbidity through the use of interaction terms.

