### Patient safety

Study staff are present in the hospital at all times (ie, 24 hours/day and 7 days/week). All adverse events are reported immediately to a study investigator and documented in a separate adverse event form. Death and withdrawal from the study unexpectedly are considered adverse events. The Institutional Review Boards and Data Safety and Monitoring Board (DSMB) review cumulative safety and study data after 30% enrolment and 60% enrolment and ad hoc as is necessary. The DSMB reports are shared with both the funding agency and investigators.

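### The printed O'Brien-Fleming cut-offs slightly exceed the stated 5% two-sided error (5.24% at equal thirds, 5.36% at 30/60/100%), and the text names the wrong type of error

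*Protocol article*

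**What the plan says.** Three places in the protocol article bear on this.

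- Sample size and power using adaptive design methods: the power statement is made "With a 95% follow-up rate and α=0.05", for 900 children.
- Statistical methodology and analysis: logistic regression is used at the interims and at the end. An O'Brien-Fleming stopping rule is adopted to "address any inflated type II error stemming from multiple comparisons". The two-sided p values and Z cut-offs for the "first interim, second interim and final analyses will be .0006 (3.438), .0151 (2.431) and .0471 (1.985"). This section does not say when the interims take place.
- Patient safety: the review boards and the DSMB "review cumulative safety and study data after 30% enrolment and 60% enrolment and ad hoc as is necessary". These are the only review times in the article.

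**The concern.** The three Z values are the thresholds for stopping early and for claiming a mortality difference at the end. Together they should use up the 5% two-sided error on which the power statement rests. Two things suggest that they do not. The values have the shape that belongs to looks at one third, two thirds and the end, whereas the stated reviews come at 30% and 60%. And the final cut-off of 1.985 is smaller than the standard three-look O'Brien-Fleming constant. The stated purpose of the rule is also wrong on its face: a boundary for repeated testing protects the type I error, not the type II error.

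**Working it through.** **Inputs.** Alpha 0.05 (sample size section); two-sided cut-offs 3.438, 2.431 and 1.985 (statistical methodology section); reviews at 30% and 60% of enrolment (patient safety section). Two assumptions are added: those reviews are the two interims, and the enrolment fraction equals the information fraction.

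**Step 1: internal consistency.** Two-sided p = 2(1 − Φ(Z)) gives 0.00059, 0.01506 and 0.04714, which match the printed .0006, .0151 and .0471. Also 1.985 × √3 = 3.438 and 1.985 × √(3/2) = 2.431. So the p values follow from the Z values, and the Z values have the O'Brien-Fleming shape for three equally spaced looks.

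**Step 2: overall error of the printed cut-offs.** Under the null hypothesis the Z statistics at information fractions t_j < t_k are jointly normal with correlation √(t_j/t_k). The overall error is the sum over looks of the probability of crossing at that look without having crossed before. Recursive numerical integration gives:

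| Looks | First | Second | Final | Total |
|---|---|---|---|---|
| 1/3, 2/3, 1 | 0.00059 | 0.01471 | 0.03711 | 0.0524 |
| 0.30, 0.60, 1 | 0.00059 | 0.01471 | 0.03826 | 0.0536 |

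Simulation of 20 million trials per schedule agrees (0.0524 and 0.0536). The first two columns are identical because t₁/t₂ = 1/2 under both schedules. The timing affects only the final column.

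**Step 3: where the excess comes from.** Solving c/√t for a total of 0.05 at equal thirds gives c = 2.004 (cut-offs 3.471 / 2.454 / 2.004), not 1.985.

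- From the constant: 5.24 − 5.00 = 0.24 points.
- From the timing: 5.36 − 5.24 = 0.12 points.
- Share from the constant: 0.24 / 0.36 = two thirds.

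**Step 4: boundaries that give 5% at 30/60/100%.**

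| Boundary | Z | p |
|---|---|---|
| Classical O'Brien-Fleming | 3.638 / 2.573 / 1.993 | .0003 / .0101 / .0463 |
| Lan-DeMets, O'Brien-Fleming-type spending | 3.929 / 2.670 / 1.981 | .00009 / .0076 / .0476 |
| Printed interim cut-offs, new final one | 3.438 / 2.431 / 2.021 | .0006 / .0151 / .0433 |

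**Step 5: cost in power.** Take 450 × 0.95 = 427.5 per arm and mortality of 14.7% versus 8.7%. The expected final Z is 0.060 / √[(0.147 × 0.853 + 0.087 × 0.913) / 427.5] = 2.741. Integrating with this drift at 30/60/100% gives power of 78.2% for the printed cut-offs, 77.9% for Lan-DeMets, 77.7% for classical O'Brien-Fleming and 77.2% for the third option. At the design rates (14.7% versus 6.1%) all four lie between 98.5% and 98.6%.

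**The case against.** The strongest reply is that the excess is about as small as the error of the approximation used to find it. The figure of 5.36% is a large-sample limit, while the planned analysis is logistic regression with low event rates. A simulation of the printed cut-offs at 30/60/100%, with 427 per arm, a Wald test (an assumption, since the article names no test) and 2 million trials per scenario, gave overall two-sided errors of 4.8%, 5.0%, 5.1% and 5.3% at common mortality of 6%, 8.7%, 10.4% and 14.7%. This stands: the realised error depends on the test and the event rate, and 5.36% should not be read as a fixed property of the trial. It does not make the printed constant correct, because the boundary is meant to hold 5% in the same large-sample sense in which it was derived.

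The link between the 30% and 60% reviews and the interim analyses is also inferred. Two reviews match two interims and no other times are given, but the article does not equate them. The 5.24% at equal thirds does not need that link.

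A reader might infer more than the article supports, in four ways:

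- **That the timing explains the excess.** It explains about one third. The cut-offs miss 5% at equal thirds too.
- **That the cut-offs are too lenient at every look.** The Lan-DeMets final cut-off is 1.981, so the printed 1.985 is slightly stricter there.
- **That the 60% threshold is itself an error.** A p value of .0101 is what the classical shape needs at that fraction, but keeping .0151 and raising the final Z to 2.021 also gives 5%. The choice is one of boundary shape.
- **That the ad hoc reviews add uncontrolled efficacy looks.** Nothing says that they involve a comparative efficacy test, and rules for unplanned looks commonly sit in an analysis plan or DSMB charter, which is not shown.

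**Conclusion.** The point holds as a minor correction. The printed cut-offs do not deliver the stated two-sided alpha of 0.05 in the large-sample calculation: 5.24% if the interims fall at equal thirds, and 5.36% if they are the reviews at 30% and 60% and enrolment tracks information. The main cause is the constant, 1.985 instead of 2.004, with a smaller contribution from the timing. Naming type II error as the target is wrong whatever the timing. An excess of 0.24 to 0.36 points is unlikely to change the trial's conclusion unless the result falls close to a boundary, but these are printed decision thresholds and they should be right.

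**What to change.** 1. State when the two interim analyses take place, and whether they are the reviews at 30% and 60% of enrolment.
2. Recompute the boundary for those times. At 30/60/100%, any one of the three sets in step 4 gives 5%. Lan-DeMets spending has the practical advantage that it adjusts if the actual information fractions differ from the planned ones.
3. Change type II error to type I error in the description of the stopping rule.

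No extra patients are needed. At 14.7% versus 8.7%, power falls by about 0.3 points with Lan-DeMets (78.2 to 77.9), 0.5 points with classical O'Brien-Fleming (78.2 to 77.7), and 1.0 point if the printed interim cut-offs are kept and the final Z becomes 2.021 (78.2 to 77.2). Either of the first two is therefore the cheaper choice.

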**Methods and analysis:**

CPAP IMPACT is a randomised clinical trial comparing bCPAP to low-flow oxygen in the treatment of severe pneumonia among high-risk children 1–59 months of age. High-risk children are stratified into two subgroups: (1) HIV infection or exposure and/or severe malnutrition; (2) severe hypoxaemia. The trial is being conducted in a Malawi district hospital and will enrol 900 participants. The primary outcome is in-hospital mortality rate of children treated with standard care as compared with bCPAP.

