#### Randomisation and blinding

Simple 1:1 randomisation is conducted at enrolment using sequentially numbered sealed opaque envelopes. Due to the nature of the bCPAP intervention this study is unblinded for study staff and caregivers.

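### The covariate-adjusted model exists only if a baseline imbalance test is significant, so its covariates are picked by chance imbalance rather than named in advance for their prognostic value

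*Protocol article*

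**What the plan says.** All references are to the protocol article.

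- **Statistical methodology and analysis, primary model.** Logistic regression is used for the primary and interim analyses, and "study arm (bCPAP vs standard care) will be the treatment variable in primary and interim outcome analyses". No covariate is named.
- **Same section, adjustment rule.** "If any significant imbalance between groups on baseline covariates is present then results of logistic regression analyses controlling for these variables" are to be produced as well. The adjusted model is thus an addition to the arm-only model and does not replace it. Neither a test level nor a covariate list is given.
- **Same section, secondary analyses.** Risk category and severe hypoxaemia enter models with an arm-by-characteristic interaction, whatever the observed balance.
- **Randomisation and blinding.** "Simple 1:1 randomisation is conducted at enrolment using sequentially numbered sealed opaque envelopes". Allocation is not balanced by risk group.
- **Sample size and power.** The planning assumptions give standard-care mortality of 30% for HIV-infected children, against 12% to 15% in the other risk groups.

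**The concern.** A significance test of baseline balance asks whether the arms differ by more than chance. After correct randomisation the answer is already known: any difference is chance. The test therefore tells us nothing about whether a covariate belongs in the model. What matters for adjustment is how strongly the covariate predicts death. A significant imbalance in a weak predictor can enter the model while a strong predictor with a non-significant imbalance stays out.

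Two things are at stake. First, the adjusted estimate, when it appears, comes from a model chosen by the data, and the article does not say how to read it if it disagrees with the primary result. Second, the usual reason to adjust, a gain in power from known predictors, is not realised, because the rule seldom brings those predictors in.

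The point concerns a rule that the article states. The missing covariate list and test level could be left to an analysis plan and are not criticised here.

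**Working it through.** **1. The plan's own power figure.** Inputs: "This study will accrue 900 children (450 children per study arm"), "We estimate true mortality rates of 14.7% with standard care and 6.1% for bCPAP cases", and "With a 95% follow-up rate and α=0.05". Analysed per arm: 450 × 0.95 = 427.5. Formula (two-sided, pooled variance under the null):

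power = Φ{ [|p1 − p2| − 1.96·√(2p̄(1 − p̄)/n)] / √([p1(1 − p1) + p2(1 − p2)]/n) }

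With p1 = 0.147, p2 = 0.061, p̄ = 0.104: Φ{(0.086 − 1.96 × 0.02088)/0.02067} = Φ(2.18) = 98.5%. The stated 99% is reproduced. At 8.7% in the bCPAP arm the formula gives 78.0% with the 5% loss and 80.1% without (stated: 80%).

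**2. Chance of a trigger under correct randomisation.** Assumptions: a 5% level and k independent covariates. P(at least one) = 1 − 0.95^k.

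- k = 4: 18.5%
- k = 10: 40.1%
- k = 20: 64.2%

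Correlated covariates would change these figures, and the article does not fix k.

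**3. What adjustment would gain, and what the trigger recovers.** Simulation of 4,000 trials per scenario:

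- 855 analysed children (900 × 0.95), simple 1:1 allocation, Wald test at the final cut-off of 1.985 (interim looks not simulated).
- Risk-group shares: hypoxaemia only 1/3; HIV-infected 2/3 × 10%; HIV-exposed uninfected 2/3 × 30%; severe malnutrition 2/3 × 60%.
- Standard-care mortality 13%, 30%, 12% and 15% respectively.
- Common odds ratio (0.087/0.913)/(0.147/0.853) = 0.553, the effect for which the article claims 80% power.
- An extra recorded predictor, expressed as a standard deviation on the log-odds scale. This is an assumption; the article gives no such strength.

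| Extra predictor (assumed SD) | Arm only | Prespecified adjustment | Adjust only for covariates imbalanced at 5% |
|---|---|---|---|
| none (planning risk groups only) | 75.6% | 75.9% | 75.4% |
| 0.5 | 75.2% | 76.6% | 75.0% |
| 1.0 | 67.7% | 72.6% | 67.8% |
| 1.4 | 58.2% | 66.8% | 58.5% |

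Rows should be compared across, not down. The conditional odds ratio is held fixed, so the unadjusted effect shrinks as the extra predictor gets stronger. The gains are 0.3, 1.4, 4.9 and 8.6 points. The triggered approach stays within 0.3 points of arm only in every row. The Monte Carlo standard error of a single power figure is √(0.756 × 0.244/4000) = 0.7 points. All methods share the same simulated trials, so differences within a row are better determined than that, but 0.3 points should be read as close to nil.

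**4. Type I error.** With no treatment effect, the rejection rates are 4.4% to 5.1% across all methods and scenarios. Taking whichever of the arm-only and triggered results is significant gives at most 5.2%.

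**5. Standard errors.** Under the alternative, the standard error of the log odds ratio rises with adjustment (0.221 to 0.223 with risk groups; 0.221 to 0.236 at SD 1.0), while the estimate moves away from zero (−0.586 to −0.596; −0.536 to −0.607). The benefit is in power, not in a narrower interval.

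**6. Room for covariates.** Expected deaths at design rates: 855 × (14.7% + 6.1%)/2 ≈ 89 at the end. At the 30% review: 0.30 × 855 ≈ 256 children, 256 × 10.4% ≈ 27 deaths. A model with arm, three risk-group terms, hypoxaemia and age has six coefficients: 89/6 ≈ 15 deaths per coefficient at the end, but 27/6 = 4.5 at the first look.

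**The case against.** The strongest defence is that the triggered model is only a supplement. The article says it is done as well, so the arm-only result is always available and is plainly the primary one. A reader might infer that the rule puts the primary conclusion or its error rate at risk, or leaves two rival primary answers. The text does not support that, and the simulated error rates show no material inflation. This part of the defence stands.

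A reader might also infer that much power or precision is being lost. The article's own figures do not support this either. HIV infection is 60 of 900 children and the other groups lie at 12% to 15%, so the risk groups are worth about 0.3 points, and power at the full design effect is already about 98.5%. Nor does an uneven HIV split do much damage. With 60 such children, the 95% range in one arm is 22 to 38. Even 38 versus 22 shifts expected mortality by only (16/450) × (30% − 13.6%) ≈ 0.6 points, against a design difference of 8.6, where 13.6% is the average of the other groups: (300 × 13% + 180 × 12% + 360 × 15%)/840. That split gives z ≈ 16/√60 ≈ 2.1, so the rule would itself adjust for it.

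The abstract's wording, "High-risk children are stratified into two subgroups", might suggest stratified allocation. The randomisation section states simple allocation, so that sentence can be read only as describing subgroups.

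Finally, the secondary interaction models do use prespecified characteristics. They address effect modification one characteristic at a time and do not supply a prespecified adjusted overall effect.

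None of this justifies the trigger. It limits what the trigger costs.

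**Conclusion.** The point holds in a limited form. The stated rule makes both the existence and the content of the adjusted analysis depend on tests that, under simple randomisation, can detect only chance. It selects covariates by imbalance instead of prognosis, and so delivers almost none of the benefit of adjustment.

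What is affected is the interpretability of the supportive analysis and a modest opportunity for power. The primary test is not affected. The 18.5% and 40% trigger probabilities rest on an assumed 5% level and independent covariates. The 0.3-point gain rests on the article's risk-group shares and mortality. Gains from about 1 point upwards rest wholly on assumed predictor strengths. This is worth correcting because the correction is cheap, not because the trial's conclusion is in danger.

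**What to change.** Delete the imbalance trigger. Prespecify one adjusted logistic model, fitted whatever the observed balance, with a short list of variables recorded at entry: risk group including HIV status, severe hypoxaemia, and age if the number of deaths allows. State in advance whether this or the arm-only model is primary, and report the other as supportive. Either choice is defensible; leaving it to the data is not.

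The cost is one paragraph of analysis text, best fixed before any comparison of outcomes by arm. No new data are needed, since these variables determine eligibility. There are two small downsides. The adjusted odds ratio is conditional on the covariates and will not equal the unadjusted one, so the text should say which is being reported. The list must also stay short at the first interim, where only about 27 deaths are expected; a reduced list or the arm-only model could be specified for that look.
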